# STUDY DESIGN

## General design

Any newly diagnosed (within 6 months) type 2 diabetic patient who is visiting tier 3, 2, or 1 hospitals, may be considered for enrollment in this study, as long as the patient meets the inclusion and exclusion criteria and is willing to sign on the informed consent form.

Enrolled patients will receive routine treatment (diet & exercise or medication) and will be asked to return to the same investigator for follow up visits at 3, 6, 9 and 12 month after the baseline visit.

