**[name] on behalf of CCMR Executive Committee**

Chairman of CCMR Executive Committee

Chief Scientific Officer

VitalStrategic Research Institute

SYNOPSIS

| Study Type | Observational, longitudinal, prospective cohort study |
| --- | --- |
| Study Subjects | Newly diagnosed type 2 diabetic (T2D) patients defined as diagnosis of T2D according to the Chinese Guideline (2010) for Type 2 Diabetes, within the past 6 months. |
| Number of Subjects | Approximately 5000 patients from nation-wide hospitals will be recruited |
| Study Location | Approximately 80 hospitals (40 tier 3, 25 tier 2, 15 tier 1) from 6 major geographic regions in China will be recruited for this study. |
| Principal Investigator | [name], Director of Endocrinology Department, Beijing University, People’s Hospital, Beijing, China |
| Investigators | Qualified internists and endocrinologists will be selected from the members of CEA and other CCMR physician networks. |

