| Inclusion and Exclusion Criteria | Inclusion criteria   - 20 years of age or older - Confirmed diagnosis of type 2 diabetes made within past 6 months - Willing to return for all follow up visits (3, 6, 9, 12 months after baseline visit)   Exclusion criteria  To help ensure sufficient rate of return for follow up in the longitudinal study, the exclusion criteria are the following:   - Patients who are currently pregnant or are breast feeding, or plan to get pregnant during the following year; - Patients who are not willing or not able to return to the same hospital for follow up visits every 3 months for one year after enrollment; - Patients who are participating in any other interventional clinical trials; - Patients who have been on diabetes medications but have no clear information regarding the medication used; - Patients who are not willing to sign informed consent form. |
| Observational endpoints | **Primary endpoint**  The overall proportion of patients whose HbA1c is less than 7%, measured at the end of one year follow up.  **Secondary endpoints**   1. The proportions of patients receiving one OAD, two OADs, > two OADs, insulin alone, insulin+one OAD, insulin+two OADs, insulin+>two OADs and by class of OADs at 3, 6, 9, and 12 months; 2. Mean duration of diet & exercise alone (t4), initial anti-diabetic treatment (ADT) (t1), initial ADT is switched or 2nd ADT is added (t2), 2nd ADT is switched or 3rd ADT is added (t3) ; (Figure 1 Treatment Pattern Diagram); 3. The proportion of patients reached the therapeutic target of glycemic control by treatment regimen and by OAD class at 3, 6, 9 and 12 months: 4. The correlation between treatment patterns and patient demographics, social-economic status, insurance, medical history, HbA1C level, type of hospital, physician years of practice, etc; 5. Incidence of microvasular diabetic complication: diabetic retinopathy, nephropathy, neuropathy, and macrovascular complications: cardiovascular events, peripheral vascular complications, and stroke, at 3, 6, 9, and 12 months; 6. Were the diabetes related clinical examinations applied such as Fundus examination and diabetic foot screening; 7. Incidence of hypoglycemia associated with various ADTs; 8. Diagnosis patterns, including the methods of diagnosis (i.e. routine physical examination, seeing doctors for other diseases, etc), and type of hospital, as well as its association with demographics and regions of residence. |

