## Inclusion criteria

- 20 years of age or older;
- Confirmed diagnosis of type 2 diabetes made within past 6 months according to the 2010 Chinese Guideline for Type 2 diabetes;
- Willing to return for all follow up visits (3, 6, 9 and 12 months after baseline visit).

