## Exclusion criteria

- Patients who are currently pregnant or are breast feeding, or plan to get pregnant during the following year;
- Patients who are not willing or not able to return to the same hospital for follow up visits every 3 months for one year after enrollment (e.g. do no reside locally);
- Patients who are participating in another interventional clinical trials;
- Patients who have been on diabetes medications but have no clear information for the drugs used;
- Patients who are not willing to sign informed consent form.

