## Measurements at Baseline and Follow-up Visits

Each patient will return to see the same physicians for follow up visits at 3, 6. 9 and 12 month after the first visit, and the following measurements will be recorded, laboratory reports will be obtained.

- Blood pressure: The subjects should be resting for at least 5 minutes prior to measurement of blood pressure. Measure the sitting or supine blood pressure, and take the mean of values of 2 continuous measurements. There should be 2 minutes interval between the 2 measurements.
- Height and body weight: Remove the shoes and socks prior to measurement, as well as wear light clothes. Formula for body mass index calculation: BMI= Body weight (kg)/Body height^2^ (m)
- Waist circumference: Remove the clothes on the waist and stand relaxed with both hands down naturally. Then use tape around the waist and adjust its location to make the tape pass the intermediate points between superior margins of hip bones at both sides and lower costal margins. Pay attention to that the tape should be parallel to the floor and cling to but no compress the skin.
- Health behavior
- Smoking history: Record the average number of cigarettes per day and smoking time. A smoker is defined as a person who smokes 1 cigarette a day on the average for at least 1 year.
- Exercise pattern: Physical inactivity means the subjects do not have frequent physical exercise (such as amount of exercise equal to that in walking for at least 20-30 minutes a day, 3-4 days a week).
- Medication: Including medication previously prescribed for glycemic control and any other concurrent medications. Record generic name, brand name, dosage, frequency, years taken, and purpose. Current and any change of medications since last recorded visit for treatment of type 2 diabetes, diabetic complications, lipid-regulation, and hypertension, including prescription drugs, OTC drugs and Chinese herbal medicines should be recorded.
- Reason for adjusting anti-diabetic medications
  1. Unsatisfactory treatment outcomes: according to FBG results, or 2-hour postprandial blood glucose, or HbA1c
  2. Adverse events: hypoglycemia, gastrointestinal reactions, edema, weight gain, change of liver or kidney functions, allergic, other discomforts.
  3. Economical reasons
  4. Self-adjustment: details will be required
- Compliances: does the patient routinely take medicines in accordance with the prescriptions, if not, the specific reasons will be required

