# OBSERVING ENDPOINTS

## Primary endpoints

The overall proportion of patients whose HbA1c is less than 7%, measured at the end of one year follow up.

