# SAMPLE SIZE AND STATISTIC EVALUATION

As this is a descriptive study, there will be no hypothesis testing. The sample size is calculated based upon a desired margin of error for the proportion of subjects reaching the target HbA1c level.

In the 2007 Chinese Guideline for Diabetes Prevention and Treatment [20], the target HbA1c level was set to be <6.5%,. However, in the newest Chinese Guideline published in November 2011 [19], the target HbA1C level has been adjusted to <7.0%, based on the evidence showing that HbA1c<7.0% is already associated with decreased incidence of diabetic complications and that further reduction of HbA1c with using more aggressive intervention might result in an increased incidence of hypoglycemia. In patients with cardiovascular complications, further reduction of HbA1C beyond 7.0% may even be associated with increased risk of CV events. On the other hand, for newly diagnosed patients, the latest guideline still recommended to aim for normal level of HbA1C (<6.5%) by using insulin or other ADT (anti-diabetic treatment) with low risk of hypoglycemia. The target HbA1C level for this study is thus set to be consistent with the guideline, i.e. 6.5%.

According to the results of the Polish ARETAEUS1 study [19], 28.9% of the patients who were diagnosed with T2D within 2 years achieved a therapeutic target of HbA1C <6.5%. Pan et al [14] reported 25.9% of T2D patients in China achieved a target glycemic control level of HbA1C <6.5%. A recently completed CCMR study showed that 30.7% of the stabilized T2D patients (diagnosed more than 6 months) in China reached this therapeutic target. We thus estimate that the proportion of newly T2D patients reaching the target of HbA1c < 6.5% in this study is approximately between 26%-31%.

Assuming a confidence level of 95%, a confidence interval of 0.05 (margin of error of +/- 2.5%), and the expected proportion (p) of 0.30, n=1,315 subjects are required. To ensure each of the three hospital tier has sufficient subjects to demonstrate the assumed proportion of patients reaching the target HbA1c <6.5%, the total sample size would be n=3,945 (1,315 x 3). Attrition is often a challenge in observational studies and three recent, large population-based observational studies of diabetes patients in China reported attrition rates ranging from 14% to 25%. Assuming an attrition rate of approximately 20% for this study, a sample size of 4,931 is required.

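### No rule governs which eligible patients are enrolled, and the target population is unstated, so the one-year proportion carries a selection bias that the ±2.5 point margin does not cover

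*Protocol*

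**What the plan says.** Protocol Section 4.1 (General design) gives the whole enrolment rule: "Any newly diagnosed (within 6 months) type 2 diabetic patient who is visiting tier 3, 2, or 1 hospitals, may be considered for enrollment", provided that the criteria are met and consent is signed. The synopsis says the same under Study Design. Neither place says in what order, or by what method, eligible patients are approached. The Protocol plans no record of eligible patients who are not enrolled.

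Two criteria then select on expected attendance. Section 4.2 requires patients to be "Willing to return for all follow up visits (3, 6, 9 and 12 months after baseline visit"), and Section 4.3 excludes "Patients who are not willing or not able to return to the same hospital for follow up visits every 3 months for one year", with living elsewhere given as an example. The synopsis states the purpose openly: "To help ensure sufficient rate of return for follow up in the longitudinal study, the exclusion criteria are the following".

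The primary endpoint in Section 6.1 is "The overall proportion of patients whose HbA1c is less than 7%, measured at the end of one year follow up". On sites, the synopsis says that "Approximately 80 hospitals (40 tier 3, 25 tier 2, 15 tier 1) from 6 major geographic regions in China will be recruited". Section 7 sizes the study for a margin of ±2.5 points in each hospital tier. The Background says that the study should give comprehensive knowledge of how newly diagnosed diabetes is currently managed.

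**The concern.** Section 7 calls this a descriptive study without hypothesis testing. Its main product is a proportion, and there is no randomised comparison in which a selection effect common to both arms would cancel. Who enters the sample therefore decides what the number means.

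If each site settles for itself which eligible patients to approach, the enrolled group can differ from the eligible group in ways related to one-year HbA1c. The practice can also differ between sites and tiers. Tier matters twice: Section 7 wants adequate precision in each tier, and secondary objective 2 lists hospital tier among the factors to be studied.

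This cannot be left to a statistical analysis plan. An enrolment rule and a tally have to be in place before the first patient is approached. Afterwards, patients who were never counted cannot be recovered.

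A second, smaller matter is the population. The setting is described as nationwide, but the criteria define a narrower group, and the Protocol never says to whom the proportion applies.

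**Working it through.** **Inputs.** From Section 7: 95% confidence, margin d = 0.025, p = 0.30, 1,315 per tier, 3,945 evaluable, 20% attrition, 4,931 enrolled. From the synopsis: 40, 25 and 15 hospitals in tiers 3, 2 and 1. From Section 9.3: six months of enrolment.

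**1. The plan's sample size.** n = z²p(1−p)/d² = 1.96² × 0.30 × 0.70 / 0.025² = 1,291. The stated 1,315 is within 2% of this, and p = 0.31, the top of the plan's expected range, gives exactly 1,315. Then 1,315 × 3 = 3,945, and 3,945 / 0.80 = 4,931. The figure is reproduced well enough. The formula contains only binomial sampling variance and treats the enrolled patients as a random sample of the population of interest.

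**2. What the margin covers.** At p = 0.30 the 95% half-width is 1.96 × √(0.21/1,315) = 2.48 points per tier and 1.96 × √(0.21/3,945) = 1.43 points overall. Both are sampling error only.

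**3. Enrolment load by tier.** Enrolled per tier = 1,315 / 0.80 ≈ 1,644. Per month: 1,644 / 6 = 274.
- Tier 3: 274 / 40 = 6.9 per hospital per month
- Tier 2: 274 / 25 = 11.0
- Tier 1: 274 / 15 = 18.3

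The ratio of tier 1 to tier 3 is 40/15 ≈ 2.7. This assumes equal enrolment across tiers, which the multiplication by three in Section 7 implies. If instead every hospital enrolled the same number (4,931 / 80 ≈ 61.6), tier 1 would supply only 15 × 61.6 ≈ 925, well short of 1,644. The stated precision per tier therefore needs unequal loads.

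**4. Form of the bias.** Let s be the share of the population of interest that is not enrolled, and D the difference in the proportion at target between enrolled and non-enrolled patients. The bias is P(enrolled) − [(1−s) × P(enrolled) + s × P(not enrolled)] = s × D. It takes the sign of D and does not shrink as n grows. The Protocol gives neither s nor D. The ranges below are my assumptions and serve only to show scale.

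| s | bias for D of 5 to 20 points | D at which bias = 1.43 | D at which bias = 2.5 |
|---|---|---|---|
| 10% | 0.5 to 2.0 | 14.3 | 25.0 |
| 20% | 1.0 to 4.0 | 7.1 | 12.5 |
| 30% | 1.5 to 6.0 | 4.8 | 8.3 |
| 40% | 2.0 to 8.0 | 3.6 | 6.2 |

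The bias may be negligible or may exceed the planned margin; the documents cannot say which. A comparison of tiers a and b is off by s(a)D(a) − s(b)D(b), which vanishes if selection acts alike in both tiers. Nothing in the Protocol ensures that it does.

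**5. Population.** Section 6.1 speaks of patients without naming a wider population. Sections 4.2 and 4.3 limit entry to those willing and able to attend the same hospital every three months for a year. The synopsis and Background frame the work as nationwide. The group that the criteria support is the narrower one.

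**The case against.** The permissive sentence opens with any eligible patient and nowhere grants investigators leave to pass some over. Free choice is inferred from a missing rule. An execution plan is cited as an appendix in Section 9.4 and is not at hand; it might contain one. This is fair as far as it goes: the point is that selection is uncontrolled in the Protocol, not that investigators are shown to choose. Likewise, no hospital's patient volume is given, so the loads in step 3 show unequal pressure on sites, not actual selection.

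The return criteria are a deliberate and disclosed choice. Admitting patients who cannot return would largely turn selection at entry into missing 12-month HbA1c, and Section 7 already allows for 20% attrition. This stands, and the criteria need not change.

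Four stronger readings are tempting but not supported:
- That the sample is enriched for adherent patients and the proportion is therefore too high. The criteria select on attendance. Adherence to treatment is a separate item, recorded at visits ("Compliances: does the patient routinely take medicines in accordance with the prescriptions"), and its relation to attendance is not documented. For patients living elsewhere the direction is not clear at all.
- That the influence of compliance is understated because its range is cut at entry. Section 7 plans Cox or logistic regression, where restricting a predictor's range costs precision but does not by itself bias the coefficient. It can shrink a correlation, and no more can be said.
- That the bias has a particular size. Any single figure from step 4 rests wholly on assumed values.
- That a log would allow the proportion to be reweighted to all newly diagnosed patients. Patients excluded by rule have no chance of enrolment, so weighting would need assumptions that a few basic variables cannot carry.

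**Conclusion.** The concern holds in a limited form. The Protocol leaves uncontrolled which eligible patients are approached at each site, and on its own figures the sites work under enrolment loads that differ about 2.7-fold between tiers. For a descriptive proportion this leaves a selection bias of unknown size and direction, which the ±2.5 point margin does not include and which a larger sample would not reduce. The load figures assume equal enrolment per tier and 20% attrition.

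A reader might go further and say that the study cannot support its primary result. The documents do not show that. Section 6.1 is not worded as a national estimate, and the proportion remains interpretable for patients at these hospitals who are willing and able to return for a year. It should not be presented as the figure for all newly diagnosed patients in China. The matter merits a change before enrolment because the remedy is cheap and cannot be applied at the analysis stage.

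**What to change.** - **Section 4.1 and synopsis, Study Design.** Replace the permissive wording with a rule such as: *every eligible patient will be invited consecutively, or all on pre-set recruitment days at high-volume sites, until the site target is met.*
- **Tally.** Keep a minimal anonymous count at each site of eligible patients not enrolled, with the reason (for example not approached, or declined) and a few basic characteristics such as age band and sex. This would also supply the counts and reasons for non-participation that item 13 of the attached STROBE checklist asks for.
- **Reporting.** Give the enrolled fraction by tier beside the proportion at target.
- **Target population.** State that the result applies to newly diagnosed patients willing and able to attend the same hospital for one year. Keep the return criteria as they are.

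The rule reduces selection among eligible patients and the tally shows how much remains. Neither removes the restriction from the return criteria, which the stated population makes plain instead.

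Cost: Protocol wording, ethics agreement for anonymous counts, slightly less convenient enrolment, and a short log at about 80 hospitals. No patients, visits or tests are added.

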## Inclusion criteria

- 20 years of age or older;
- Confirmed diagnosis of type 2 diabetes made within past 6 months according to the 2010 Chinese Guideline for Type 2 diabetes;
- Willing to return for all follow up visits (3, 6, 9 and 12 months after baseline visit).

## Exclusion criteria

- Patients who are currently pregnant or are breast feeding, or plan to get pregnant during the following year;
- Patients who are not willing or not able to return to the same hospital for follow up visits every 3 months for one year after enrollment (e.g. do no reside locally);
- Patients who are participating in another interventional clinical trials;
- Patients who have been on diabetes medications but have no clear information for the drugs used;
- Patients who are not willing to sign informed consent form.

# STUDY PROCEDURE

## Baseline Measurements

- Demography: Age, gender, residential region.
- Diabetes history and related symptoms: Duration or diagnosis (must be < 6 months), how was diagnosis made (using the 2010 Chinese Guideline for Diabetes Prevention and Treatment [19]) , signs and symptoms.
- Diagnostic pathways:
  1. Seeking health care due to diabetic symptoms
  2. Already found an increased blood glucose once, and confirmed by a second test
  3. Seeking health care due to other diseases
  4. Self-demanded lab tests
  5. Participating in an epidemiological study / campaign
- Screening methods for diabetes (could be singular or multiple choices):
  1. OGTT test
  2. “Bun test”
  3. Urine glucose
  4. Others
- Diagnostic methods for diabetes* (reference table 1), diabetic symptoms plus:
  1. Random blood glucose (the blood glucose level at any time during a day without knowing the time of last meal)
  2. FBG (fasted for at least 8 hours without calories intake)
  3. 2-hour postprandial blood glucose
- Diabetics symptoms: thirsty, constant hunger, frequent micturition, obvious weight loss, fatigue, prone to inflammation, blurred vision, numbness/pain, leg or foot ulcers, skin itching, acute complications such as ketosis, hyperosmolar coma, *etc.*
- The hospitals and departments where diabetes was diagnosed:
  1. Tier 1 hospital
  2. Tier 2 hospital: endocrinology dept., internal medicine dept.
  3. Tier 3 hospital: endocrinology dept., internal medicine dept.
- Disease history:
  1. Diabetic complication history: the acute or chronicle diabetic complications at or after the diagnosis, including ketosis, hyperosmolar coma, HHS, micro blood vessels lesions (retinal lesions, nephrological diseases, peripheral neuropathy).
  2. Medical history and co-morbidity: Including any major medical procedure or surgery occurred within the last 12 months, any major co-morbidity (e.g. cardiovascular disease, renal disease, other diabetic complications, cancer, etc).
- Family history: Family history of diabetes and cardiovascular diseases
- Education level and knowledge about T2D: Highest formal education received as well as response to simple questionnaire assessing the level of knowledge about T2D.
- Social-economic background: Employment status, marital status, monthly income, insurance type and coverage.
- Questionnaire for diabetes knowledge assessment
- Quality of life assessment (repeated at the last visit)

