## Secondary endpoints

The secondary endpoints of this study include the following;

1. The proportions of patients receiving one OAD, two OADs, > two OADs, insulin alone, insulin+one OAD, insulin+two OADs, insulin+>two OADs and by class of OADs at 3, 6, 9, and 12 months;
2. Mean duration of diet & exercise alone (t_4_), initial anti-diabetic treatment (ADT) (t_1_), initial ADT is switched or 2^nd^  ADT is added (t_2_), 2^nd^ ADT is switched or 3^rd^ ADT is added (t_3_) ; (Figure 1 Treatment Pattern Diagram);
3. The proportion of patients reached the therapeutic target of glycemic control by treatment regimen and by OAD class at 3, 6, 9 and 12 months:
4. The correlation between treatment patterns and patient demographics, social-economic status, insurance, medical history, HbA1C level, type of hospital, physician years of practice, etc;
5. Incidence of microvasular diabetic complication: diabetic retinopathy, nephropathy, neuropathy, and macrovascular complications: cardiovascular events, peripheral vascular complications, and stroke, at 3, 6, 9, and 12 months;
6. Were the diabetes related clinical examinations applied such as Fundus examination and diabetic foot screening;
7. Incidence of hypoglycemia associated with various ADTs;
8. Diagnosis pattern: to assess the methods of diagnosis (i.e. routine physical examination, seeing doctors for other diseases, etc), and location of diagnosis, demographic information of the patients and the regions of residence;
9. Quality of life assessment (baseline and the last visit);
10. Resource consumption patterns based on the information collected on the cost of medications, cost of diagnostic test and other relevant [procedure.

Figure 1 Treatment Pattern Diagram

[figure not shown]

T1 = duration between diagnosis and initiation of (single) treatment regime， T2 = duration between initiation of single treatment regime and duple regime， T3 = duration between initiation of duple treatment regime and multiple regime

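### The diagnostic-pathway list mixes reasons for being tested with a confirmation step and omits routes named in objective 6 and endpoint 8, so the diagnosis-pattern proportions can be ambiguous

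*Protocol*

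**What the plan says.** Protocol section 5.1 (Baseline Measurements) gives five numbered diagnostic pathways. Option 1 is attendance because of symptoms. Option 2 reads "Already found an increased blood glucose once, and confirmed by a second test". Option 3 is a visit made for another illness, option 4 a test that the patient asked for, and option 5 detection through a survey or campaign.

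The list has no category for other routes. It does not say whether one or several answers may be given, or which takes precedence when two apply. The next list in the same section does carry a choice rule: "Screening methods for diabetes (could be singular or multiple choices". The glucose measurement behind the diagnosis is a separate item, introduced as "Diagnostic methods for diabetes* (reference table 1), diabetic symptoms plus".

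The pathway item serves secondary objective 6 (section 3.2), which asks how diagnosis came about. Its examples are routine physical examination, health screening, diabetic symptoms and consultation for another disease. It also serves secondary endpoint 8 (section 6.2): "Diagnosis pattern: to assess the methods of diagnosis (i.e. routine physical examination, seeing doctors for other diseases, etc". The synopsis version of endpoint 8 adds the association of the diagnosis pattern with demographics and region of residence.

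**The concern.** Objective 6 asks by what route patients are detected. Options 1, 3, 4 and 5 answer that question. Option 2 answers a different one, namely whether a raised value was repeated, and it leaves open what led to the first measurement. A patient whose raised glucose came to light at a visit for another disease and was then confirmed satisfies options 2 and 3 at once.

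The list also does not match the objective it serves. A patient found at a routine check-up has no option worded for that route, and option 2 is a natural place to put such a patient. Once that happens the route is not in the data, and no later analysis can recover it.

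At stake is the distribution of detection routes and its comparison across patient groups and regions. About 80 hospitals in three tiers and six regions will apply the list. Each hospital sits within one tier and one region, so a local coding habit could show up as a regional or tier difference in how diabetes is found.

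**Working it through.** The protocol states no figure on this point, so the check is mainly a comparison of texts.

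**Step 1: what each option records** (section 5.1)

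| Option | Gives the reason for testing? | Gives a test sequence? |
|---|---|---|
| 1 Symptoms | Yes | No |
| 2 Raised once, then confirmed | No | Yes |
| 3 Other disease | Yes | No |
| 4 Self-requested test | Yes | No |
| 5 Study or campaign | Yes | No |

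Option 2 is the only one of its kind. Nothing in its wording excludes a first value that arose through option 3, 4 or 5.

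**Step 2: do the options cover the routes asked for?** (sections 3.2 and 6.2 against 5.1)

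| Route | Objective 6 | Endpoint 8 | Option in 5.1 |
|---|---|---|---|
| Routine physical examination | Named | Named | None so worded |
| Health screening | Named | Not named | None so worded; option 5 may take in part of it |
| Diabetic symptoms | Named | Not named | Option 1 |
| Visit for another disease | Named | Named | Option 3 |

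Of the two routes that endpoint 8 gives as examples, one has no matching option.

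**Step 3: is there a rule for overlaps?** The screening-methods list states one. The pathway list states neither single choice, multiple choice nor precedence.

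**Step 4: what the overlap would do, under an assumption.** Let q be the share of patients who fit option 2 and exactly one other option. The documents do not give q, so 5% to 30% is assumed here for illustration only. The item is recorded at baseline, so the planned enrolment of 4,931 (section 7) is the base.

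- Patients whose category is open = q × 4,931: 0.05 × 4,931 ≈ 247; 0.10 × 4,931 ≈ 493; 0.20 × 4,931 ≈ 986; 0.30 × 4,931 ≈ 1,479.
- With one answer per patient, the share in option 2 can move by up to q, depending only on how sites resolve the overlap. The other options together move by the same amount in the opposite direction.
- With several answers allowed, and every option that applies ticked, the shares add to 100% + q, that is 105% to 130%. That is overlap and not an error, and no route is lost for these patients.

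Step 4 does not cover check-up patients who fit option 2 and no other option. Their route goes unrecorded under either rule, and the documents give no figure for their number.

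**The case against.** The strongest reply has four parts.

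First, option 2 can be read as a route of its own: the patient attends because of an earlier raised value and is then confirmed. That reading is fair, and it defeats any claim that option 2 overlaps every other pathway. A symptomatic patient in particular need not fit option 2, because section 5.1 records diagnosis as symptoms plus a glucose measurement and states no second test there. The reading does not remove the problem, however. The origin of the earlier value is the route of detection, and it remains unrecorded.

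Second, a reader might infer from the silence on choice that one answer is forced, and hence that the endpoint is miscounted. The documents do not support this. The symptom list in the same section carries no choice rule either, yet patients plainly may have several symptoms. The eCRF, which would show how the item is answered, is not at hand. This part stands: a miscount is possible but not shown.

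Third, a reader might conclude that screening and chance detection are understated, on the ground that patients without symptoms are the ones who need a second test. The protocol text states no second-test rule, and the diagnostic table it refers to is not in the text. The direction of any bias therefore cannot be asserted.

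Fourth, this is one of ten secondary endpoints in a study that plans no hypothesis testing, and counting rules commonly belong to the analysis plan. The limited reach is conceded. A counting rule, however, cannot restore a route that was never collected. Section 9.1 has investigators enter the data that the protocol specifies, so the protocol's own list matters.

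**Conclusion.** The point holds in a limited form. The pathway list combines four reasons for testing with one confirmation sequence, which can be true together with another option and leaves the origin of the first raised glucose unrecorded. It has no option worded as routine physical examination or health screening, which the objective names. Endpoint 8 proportions, and their associations with demographics and region, can therefore be ambiguous and depend on how sites code.

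Neither the size nor the direction of the effect follows from the documents. The 5% to 30% overlap above is an assumption that shows the mechanism and does not estimate its extent. The primary endpoint and the sample size are untouched. The case for acting is that the missing route cannot be recovered after data collection, while the correction is small.

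**What to change.** In section 5.1 and the eCRF:

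- Remove option 2 from the pathway list and record confirmation by a repeat glucose test as a separate yes/no item.
- Reword the pathway item as *how was the first raised glucose found*.
- Add options for routine physical examination / health screening and for other, so that the list matches objective 6 and endpoint 8. Removing option 2 without this step would leave check-up patients with no fitting answer.
- State whether one or several answers are allowed.
- Compute endpoint 8 from the reworded item.

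The cost is a small change to one baseline eCRF item and one added yes/no field, with no extra visit or test.
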